**Objective:**

This paper describes the protocol for a single-blind, parallel-group randomized controlled trial that aims to investigate the effectiveness and cost-effectiveness of a home-based multifactorial program targeting fall risk factors among people aged 60 years and over who have fallen at least twice in the past 12 months (the MAGIC trial).

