### Outcome Measures

#### Overview

Assessments will be conducted at participants’ homes at baseline, after 16 weeks of the intervention, and at 6 weeks and 1 year post trial completion. The volunteers will be instructed to wear comfortable clothing, closed shoes, not to perform vigorous exercises the day before the assessment, and to wear hearing or visual aids if needed.

Baseline assessments include sociodemographic measures (age, sex, race, marital status, years of schooling, living alone, and income) and general health (BMI; medication use; morbidities; foot problems including dryness of skin, calluses, fissures, open ulcers, and deformities; history of falls, hospitalizations, level of physical activity measured with the Modified Baecke Questionnaire for the Elderly; general health assessed with the Self-Rated Health questionnaire; functional activities evaluated with the Lawton-Brody Scale; and risk of fracture measured with the Fracture Risk Assessment Tool—FRAX).

Primary and secondary outcomes will be reassessed after 16 weeks of the intervention and at the posttrial 6-week follow-up. In addition, after 16 weeks of the intervention, satisfaction and adherence to the intervention will also be assessed among the IG participants. Prospective falls will be collected from baseline to 1-year follow-up. The economic health assessment will be carried out for the period up to the posttrial 1-year follow-up.

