#### Secondary Outcome Measures

Secondary outcomes are falls, physical function (muscle strength of lower limbs, balance, and mobility), mental functions (cognition, depressive symptoms, and fear of falling), fall risk, safety at home, feet and footwear, satisfaction with and adherence to the intervention, and health care costs.

Prospective falls will be collected from baseline to 1-year follow-up using falls calendars and monthly telephone calls. Muscular strength of hip, knee, and ankle joints will be evaluated using the Lafayette dynamometer. In addition, muscle strength, mobility, and balance will be assessed with the Brazilian version of the Short Physical Performance Battery (SPPB). The SPPB consists of 3 tests: Balance Test, Gait Speed Test, and Chair Stand Test [14]. The scores range from 0 to 4, and the total ranges from 0 to 12 points, with higher scores indicating better lower limb function [14]. Balance will also be assessed with the MiniBest test, which has a total score of 28 points, and higher scores indicate better balance [15].

Cognition will be assessed with Addenbrooke’s Cognitive Examination-Revised screening battery, which has a maximum score of 100 points, with a score of ≤78 points indicating cognitive impairment [16]. Digit Span Forward will be used to assess attention and immediate memory deficits (indicated by scores less than 6 points) and Digit Span Backward for measuring attention and working memory deficits (indicated by scores less than 4 points) [17]. To assess depressive symptoms, the Geriatric Depression Scale will be used. Higher scores on this 15-point scale indicate a greater risk of depressive symptoms. The Falls Efficacy Scale-International will be used to assess fear of falling [18]. A total score of ≥23 points is associated with occasional falls, and a score of >31 is associated with recurrent falls [18].

Fall risk will be assessed with the Falls Risk Assessment Tool. The score varies from 0 to 5 points, with a score of 3 or more points indicating a high risk of falls [19]. Regarding home safety, the Home Falls and Accidents Screening Tool will be used. The maximum score is 25 points, and higher scores are indicative of a greater risk of falls and home accidents [20].

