For feet and footwear, the Manchester Foot Pain and Disability Index will be used. A total score of ≥2 points indicate disability associated with foot pain [21]. The tactile sensitivity of feet will be assessed using the 10-gram Semmes-Weinstein monofilament on hallux, the second and fifth metatarsals, 3 points of the forefoot, and 1 point of the midfoot and heel. Flexibility (dorsiflexion and plantar flexion) will be assessed by a goniometer. The characteristics of footwear that the volunteers usually wear at home and when they get up at night will be documented.

After 16 weeks, adherence to the case management program will be assessed by diary entries. Adherence of ≥70% to recommendations will be considered satisfactory [22,23]. In addition, questionnaires will be used to assess reasons for adhering or not adhering to treatment. The prevalence of each recommendation offered in the case management and adherence to these recommendations will also be assessed, using a 3-point scale (total adherence, partial adherence, and nonadherence) [24]. To assess satisfaction of the intervention after 16 weeks, a questionnaire based on the Short Assessment of Patient Satisfaction will be used [25]. A question will be added about the satisfaction of overall care (“How would you rate the health care you received in the past 16 weeks?”), with scores ranging from 0=worst possible care to 10=best possible care.

For economic analyses, the incremental cost effectiveness ratio will be calculated as the difference between the total cost of the IG and that of the CG. Furthermore, the use of health services will be analyzed. The EuroQol-5D is used in many cost-effectiveness studies, which allows the comparison of effects generated by interventions for any disease. Its score ranges from 1 to 3 for each item, allowing 243 different health profiles [26,27].

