## Discussion

The MAGIC trial aims to provide rigorous direct evidence about the effectiveness and cost-effectiveness of a home-based multifactorial program targeting fall risk factors among people aged 60 years and over who have fallen at least twice in the past 12 months. We hypothesize that the IG presents better awareness of fall risk and positive behavior change in reducing fall risk factors identified by case management, thus decreasing new episodes of falls with an increasing volume of physical activity after the 16-week intervention compared to the CG; in addition, we expect that community older people in the IG will continue to show the positive results obtained after the 6-week follow-up compared to the CG.

The strengths of this MAGIC study are the follow-up of individualized case management that offers greater attention to the older people in the home environment and includes the family or caregiver in the action plan for behavior change in order to reduce the identified risk factors for falls. In addition, the program offers monitoring of the older people by a physical therapist to implement a protocol for safe physical activities at home.

The researchers may encounter some limitations during this randomized controlled trial, including difficulties in recruitment, restrictions on home visits owing to the COVID-19 pandemic, and poor compliance with the recommendations proposed by the case managers. If needed, potential solutions will be the use of remote assessments by video and telephone calls and the inclusion of additional recruitment sites.

The findings of this study may provide reliable and valuable information about the effectiveness of case management for increasing fall risk awareness and reducing fall risk in older people. This study protocol detailed the design and methodology of the research to support the transparency of results. This may also assist the design of future studies.

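### The incremental cost-effectiveness ratio is defined as a cost difference with no effect to divide by, so the calculation as written does not answer the cost-effectiveness aim

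*Protocol article*

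**What the plan says.** The Abstract (Objective) says that the trial "aims to investigate the effectiveness and cost-effectiveness of a home-based multifactorial program targeting fall risk factors". The Discussion repeats the aim more strongly: the trial "aims to provide rigorous direct evidence about the effectiveness and cost-effectiveness of a home-based multifactorial program".

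The only formula for the economic analysis is in Methods, Secondary Outcome Measures: "the incremental cost effectiveness ratio will be calculated as the difference between the total cost of the IG and that of the CG". The same paragraph adds that use of health services will be analysed, and then describes the EuroQol-5D in general terms: "The EuroQol-5D is used in many cost-effectiveness studies, which allows the comparison of effects generated by interventions for any disease". On scoring it says "Its score ranges from 1 to 3 for each item, allowing 243 different health profiles".

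The list of secondary outcomes that opens the section ends with "satisfaction with and adherence to the intervention, and health care costs"; quality of life and utility are not on it. The Statistical Analysis section contains no economic analysis. The Abstract and the Outcome Measures Overview give the economic evaluation a horizon, the 1-year follow-up, but no effect measure.

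**The concern.** A cost-effectiveness ratio compares what is spent with what is gained. The stated formula contains only the first half. Followed literally, it yields a number labelled as a cost-effectiveness ratio that cannot distinguish a programme with a large benefit from one with none, or from one that does harm.

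The label makes this worse than a plain omission, because a reader of the results would take the figure for a cost per unit of effect. The missing denominator also leaves the choice of effect open. Falls, the EuroQol-5D and the awareness score would all be available, so the choice could be made after the results are known.

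This is not a detail that an article leaves to a fuller document. The article chose to give the definition, and the definition describes a different quantity.

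**Working it through.** The article gives no costs, effects, willingness-to-pay threshold or planned ratio, so there is no figure of its own to reproduce. The check is on the definition.

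**1. Units**

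- Stated quantity (Secondary Outcome Measures): Cost(IG) − Cost(CG). Unit: currency.
- Ratio the name refers to: [Cost(IG) − Cost(CG)] / [Effect(IG) − Effect(CG)]. Unit: currency per unit of effect.

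The stated quantity is the numerator alone.

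**2. Search for a denominator elsewhere**

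| Place | Economic content | Effect named for the ratio? |
|---|---|---|
| Abstract, Objective; Discussion | Cost-effectiveness as an aim | No |
| Abstract, Methods; Outcome Measures, Overview | Horizon up to the 1-year follow-up | No |
| Secondary Outcome Measures, opening list | Health care costs | No |
| Secondary Outcome Measures, economic paragraph | Cost difference, service use, EuroQol-5D | No; EuroQol-5D not linked to the formula |
| Statistical Analysis | None | No |

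The EuroQol-5D description is arithmetically sound (5 items at 3 levels give 3^5 = 243 profiles). However, it counts profiles and mentions neither a utility index nor QALYs.

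**3. What the omission does to the answer**

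The figures below are assumed, for illustration only. The cost difference is held at 500 currency units.

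| Assumed effect difference | Planned figure | Correct ratio |
|---|---|---|
| 0.05 | 500 | 500 / 0.05 = 10,000 per unit |
| 0.01 | 500 | 500 / 0.01 = 50,000 per unit |
| 0.001 | 500 | 500 / 0.001 = 500,000 per unit |
| −0.02 | 500 | 500 / (−0.02) = −25,000: costlier and worse, so dominated |

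The planned figure is the same in every row. The correct ratio varies 50-fold across the first three rows (500,000 / 10,000), and the last row reverses the conclusion.

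**4. Does a usable effect exist over the cost horizon?**

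- Falls: yes. The Overview and Secondary Outcome Measures both say that they are collected prospectively from baseline to the 1-year follow-up.
- EuroQol-5D: unclear. One Overview sentence says "Primary and secondary outcomes will be reassessed after 16 weeks of the intervention and at the posttrial 6-week follow-up", with no mention of 1 year. The same section also schedules home assessments at 1 year and runs the economic assessment to 1 year. The EuroQol-5D appears only in the economic paragraph, and the article does not say which rule governs it.

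**The case against.** The strongest reply is that this is a compressed sentence and not a decision to ignore effects. The article uses the full name of the ratio and introduces the EuroQol-5D two sentences later as a way to compare effects. It also collects falls and service use. A health economist would probably supply the denominator unprompted. This stands as a reading of intent, and it makes the repair easy. It does not make the stated formula right, and it does not settle which effect was meant.

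The reply also rightly rules out several stronger readings that a reader might infer:

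- *That effect measurement stops at the 6-week follow-up while costs run to 1 year.* The reassessment sentence taken alone suggests this. The same section, however, schedules assessments at 1 year, collects falls to 1 year and carries the economic assessment to 1 year. At most, the timing of the EuroQol-5D is unclear.
- *That the programme will almost surely cost more, so the figure is bound to mislead.* No costs are given. The formula uses total cost, which could include savings from less use of services, so the direction is unknown.
- *That the trial will report nothing but cost.* Service use is to be analysed, and falls and the clinical measures are outcomes in their own right.
- *That missing detail on QALY calculation, the ranking of effect measures or the method for intervals is itself an error.* A condensed article may leave these to a fuller plan.

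Finally, cost-effectiveness has no part in the primary outcome or the sample size calculation, so the reach of the error is limited.

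**Conclusion.** The definition is wrong as written. It gives incremental cost in currency under the name of a ratio, no section supplies the effect, and the calculation therefore does not answer the cost-effectiveness aim in the Objective and the Discussion. A reader might conclude that the trial cannot answer that aim at all. The article does not support this, since falls are collected over the horizon used for costs and a correct ratio can be formed from them.

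No size can be put on the error from the trial's own figures. The illustration shows that one planned value is compatible with ratios from 10,000 to 500,000 per unit of effect and with dominance, given an assumed cost difference of 500 and assumed effect differences. The conclusion that the formula is wrong does not depend on those assumptions. The consequence is confined to a secondary economic analysis.

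**What to change.** Replace the sentence in Secondary Outcome Measures with a definition of this form:

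ICER = (mean total cost IG − mean total cost CG) / (mean effect IG − mean effect CG), both taken over the same period up to the 1-year follow-up.

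Name the effect before analysis:

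- **Falls avoided:** no new data are needed. Code the effect so that a positive difference is a benefit, that is, mean falls CG − mean falls IG.
- **QALYs from EuroQol-5D utilities:** state that the instrument is administered through the 1-year follow-up, and reconcile this with the reassessment sentence in the Overview.

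Report the ratio with a measure of uncertainty. The method can be left to the analysis plan.

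The cost is one corrected sentence and one named effect. If QALYs are chosen and the EuroQol-5D is not already given at 1 year, add one short questionnaire at an assessment already scheduled. The primary analysis and the sample size are unaffected.

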### Power and Sample Size

For the primary outcome (fall risk awareness), the sample size was calculated using the G*Power 3.1 software, based on type of study design (2-way ANOVA), type I error of 5%, statistical power of 80%, moderate effect size (0.20), and number of groups (n=2). This revealed that a total sample size of 42 is required. Allowing for 20% dropout, we will recruit a sample size of 60 people.

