### Statistical Analysis

For statistical analysis, a significance level of 5% will be adopted, and SPSS (version 22.0; IBM Corp) will be used. The analysis will be performed by intention to treat. The Kolmogorov-Smirnov normality test will be applied for all continuous variables to verify data distribution. To compare groups with regard to clinical and sociodemographic characteristics, the chi-square association test and the independent samples *t* test will be used. To test the interaction between groups and assessments, a 2-way, repeated measures ANOVA will be used. If an interaction is identified, simple main effects analyses will be performed, with adjustment for multiple comparisons (Bonferroni correction). To verify which factors influence adherence to the intervention (frequency of ≥70%), a univariate logistic regression analysis will be used. To check which factors influence satisfaction with the intervention, a simple linear regression analysis will be applied.

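### The sample size reproduces, but the effect of 0.20 it calls moderate is about 0.85 SD in the planned interaction test; power for a half-SD effect is well below 80%

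*Protocol article*

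**What the plan says.** The Power and Sample Size section sizes the trial on the primary outcome: "For the primary outcome (fall risk awareness), the sample size was calculated using the G*Power 3.1 software". The design is given as a two-way ANOVA with a 5% type I error, and the remaining inputs are "statistical power of 80%, moderate effect size (0.20), and number of groups (n=2"). The result is "This revealed that a total sample size of 42 is required", followed by "Allowing for 20% dropout, we will recruit a sample size of 60 people".

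Two other sections identify the test. The Statistical Analysis section says "To test the interaction between groups and assessments, a 2-way, repeated measures ANOVA will be used". The Overview of the outcome measures says "Primary and secondary outcomes will be reassessed after 16 weeks of the intervention and at the posttrial 6-week follow-up", which with baseline makes three measurements of the primary outcome. The Discussion expects the benefit seen at 16 weeks to be kept at the 6-week follow-up.

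The article does not name the effect-size index. It gives no SD and no difference in questionnaire points.

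**The concern.** A reader of the sample size paragraph is told that the trial has 80% power for a moderate effect. In an ANOVA, a standardised effect of 0.20 has no fixed meaning in SD units, because the meaning depends on which term is tested. In a plain comparison of two means f = d/2, so 0.20 would be a difference of 0.40 SD and the label would be reasonable. That comparison needs about 200 people, not 42. The total of 42 arises only when 0.20 is attached to a group-by-time interaction, where the same number stands for a much larger difference between arms.

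At stake is how the primary result can be read. If the power statement is taken at face value, a non-significant interaction could be presented as evidence against a moderate benefit that the trial was not sized to detect.

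**Working it through.** **Inputs from the article.** Alpha 0.05, power 80%, effect size 0.20, k = 2 groups, N = 42, 60 recruited with 20% dropout (60 × 0.8 = 48 completers), interaction test, m = 3 assessments.

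**Assumptions.** The effect size is f, the index G*Power uses for ANOVA. The correlation between assessments is r = 0.5 and sphericity holds; neither is stated. A moderate effect is taken as 0.5 SD.

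**1. Reproduce 42.** For the within-between interaction:

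- λ = f²·N·m/(1 − r), df1 = (k − 1)(m − 1), df2 = (N − k)(m − 1).
- λ = 0.04 × 42 × 3/0.5 = 10.08, df = 2 and 80, power 0.803.
- N = 40 gives 0.782, so 42 is the smallest balanced total reaching 80%.

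This setting is the most plausible but not the only one: m = 2 with r = 0.6 also gives 42, and m = 4 with r = 0.4 gives 44 (power 0.798 at 42). Tests other than the interaction do not come close. The between-group repeated-measures test needs 134, and a factorial ANOVA with one numerator degree of freedom needs about 200.

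**2. Convert 0.20 to SD units.** Take arm differences (0, d, d): equal at baseline by randomisation, with the effect sustained as the Discussion expects.

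- The mean difference is 2d/3, so the deviations are −2d/3, d/3, d/3.
- Each is split equally between the arms, giving cell effects of size d/3, d/6, d/6.
- f² = (1/3)(d²/9 + d²/36 + d²/36) = d²/18, so f = d/√18.
- d = 0.20 × 4.243 = **0.85 SD**.

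If the effect halves by the second follow-up, f = d/√24 and d = 0.98 SD. The other settings near 42 give 0.80 SD (m = 2) and 0.92 SD (m = 4). A simulation of 20,000 trials at 0.849 SD with N = 42 gave 80.7% power.

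**3. Power for 0.5 SD.** f = 0.5/√18 = 0.118 and f² = 0.01389. At r = 0.5, λ = 0.01389 × N × 3/0.5, which is 3.5, 4.0 and 5.0 for N = 42, 48 and 60.

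| Analysed | r = 0.3 | r = 0.5 | r = 0.7 |
|---|---|---|---|
| 42 | 27% | 36% | 55% |
| 48 | 30% | 40% | 62% |
| 60 | 37% | 49% | 72% |

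Simulation at N = 42, r = 0.5 gave 35.7%. At r = 0.5, 80% power for 0.5 SD needs about 118 analysed.

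**4. Detectable difference at 80% power.** At r = 0.5 it is 0.85 SD with 42, 0.79 SD with 48 and 0.70 SD with 60. With 48, the required f is 0.186, so λ = 0.186² × 48 × 3/0.5 ≈ 9.96. Holding λ fixed:

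- r = 0.3: f = √(9.96 × 0.7/144) = 0.220, d = 0.93 SD.
- r = 0.7: f = √(9.96 × 0.3/144) = 0.144, d = 0.61 SD.

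Recruiting 60, rather than the 53 that 20% dropout requires (42/0.8 = 52.5), narrows the gap but does not close it.

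**The case against.** The best defence is that the plan does what it says. The only effect it states numerically is 0.20, and for f = 0.20 the power holds: 80% at 42, and about 86% at 48 and 93% at 60. The half-SD benchmark is not in the article; it is one reading of a single adjective. This stands in part. A reader might infer that 42 is a miscalculation, and the reproduction above shows that it is not.

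A second defence is that the correlation entered in G*Power is the kind of setting an article leaves to the full protocol. That also stands: its absence alone is not a fault. It does limit what can be claimed. A reader might infer that the trial had well under even odds of finding a half-SD effect. At correlations around 0.5 or lower and 48 completers that is so, but at 0.7 power is 62% with 48 and 72% with 60, so it cannot be stated without the correlation.

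Third, nothing in the article says that a null result would be read as excluding a moderate effect. That is right; it is a risk of interpretation, not a stated intention.

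What none of this answers is the label. The article attaches the word moderate to a figure which, in its own planned test, stands for a difference of 0.80 SD or more under every setting examined that gives a total of about 42.

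**Conclusion.** The point holds as a fault in effect-size labelling and in the power statement. The printed claim of 80% power for a moderate effect describes a property that the design does not have. At 42 analysed, the effect with 80% power is about 0.85 SD when the benefit is sustained, and 0.98 SD when it halves by the second follow-up. No combination of 42, 48 or 60 analysed with a correlation of 0.3 to 0.7 reaches 80% power for 0.5 SD.

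The conversion to 0.85 SD rests on f as the index, three assessments and the sustained pattern. The power figures rest in addition on sphericity and the correlation shown, and on 0.5 SD as the meaning of moderate. The point is less than critical: it changes neither the number recruited, nor the conduct of the trial, nor the planned test. It does govern how a null primary result may be interpreted.

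**What to change.** Keep the target of 60. In the power statement:

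- Remove the word moderate, name the index as f for the group-by-assessment interaction, and list the number of assessments and the correlation actually entered in G*Power.
- State the between-group difference for which 48 completers and three assessments give 80% power at that correlation: about 0.8 SD if it was 0.5, 0.93 SD if 0.3, 0.61 SD if 0.7, assuming the effect is sustained over both later visits.
- Convert that difference to points on the 0–32 awareness questionnaire with the sponsor's own SD, since the article gives none.
- Add that a non-significant interaction does not exclude a half-SD effect, and report the between-arm difference with its confidence interval.

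The cost is a rewritten paragraph with a less favourable figure, and retrieval of the G*Power settings and an SD. No extra participants are needed; the Results section already reports 52 recruited.
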